## Abstract

Preterm birth (PTB) is the main cause of perinatal and neonatal morbidity and mortality worldwide. Widespread implementation of guidelines for early identification and management of patients at risk for adverse pregnancy outcomes is still feeble. This work aims to implement a simple and low-cost bundle to access and manage major modifiable risk factors for PTB. We included first trimester pregnant women seen at Health Units from Jaú – SP, Brazil, where PTB prevalence ranges from 13,4% to 18%. The protocol is based on three aspects: a questionnaire to access smoking status and clinical history; Gram staining and of vaginal microbiota evaluation using Nugent’s criteria and evaluation of cervical infections; and transvaginal ultrasound. Pregnant women who smoke and are willing to quit will be treated with auricular acupuncture and referred to a support group if necessary. All patients will be advised on intimate hygiene habits, and those with dysbiosis will be treated. Cervical length will be accessed using transvaginal ultrasound, and those diagnosed with cervical shortening will be treated with vaginal progesterone. This study highlights the importance of implementing active measures to reduce PTB risk factors in a high prevalence setting.

## Background

Preterm birth (PTB), defined as birth before 37 weeks of gestation, is associated with perinatal morbidity and mortality worldwide. Preterm newborns are more likely to have short- and long-term complications, such as neurological impairment and increased susceptibility to infections, which can lead to irreversible sequelae and reduced quality of life [1].

Worldwide, the prevalence of PTB is approximately 11% [1], and Brazil is one of the most affected countries, with over 308,700 children born preterm every year, accounting for a preterm birth rate of 11.5%. In São Paulo state, 12% of births in 2023 were preterm, and a higher percentage was reported in the municipality of Jaú, where this adverse outcome affected 13.5% of all pregnancies [2].

PTB is a syndrome of multifactorial etiology with significant activation of inflammatory, oxidative stress, and senescence pathways [3]. PTB prevention should be a priority in public health policies; however, despite all the scientific and clinical efforts to fully elucidate and prevent PTB, protocols for early identification and effective management of women at risk have not yet been well-defined or effectively implemented, especially in Brazil. The main barrier to the implementation of such strategies is the gap in knowledge and communication between researchers, health professionals, and policymakers. In this context, three modifiable risk factors stand out for their well-established association with PTB: smoking habit, vaginal dysbiosis, and cervical shortening [4–9].

Smoking is a strong predictor of spontaneous preterm labor. Smoking during pregnancy has been associated with numerous adverse outcomes, including low birth weight, intrauterine growth restriction, prematurity, and infant mortality, due to heightened levels of inflammation and oxidative stress [4]. It is important to emphasize that smoking may be considered as a modifiable risk. In an epidemiological study based on national databases in the United States, Soneji et al. [4] observed that smoking cessation was associated with a relative reduction in the risk of PTB up to 23%, especially if the habit was stopped early in pregnancy. The authors also observed a dose-responsedose–response effect, with the risk of PTB being directly proportional to the number of cigarettes consumed. There are currently some strategies available to control smoking, such as pharmacological treatment, group support, and acupuncture. Studies suggest that auricular acupuncture can contribute to combating smoking through points that promote a reduction in anxiety and withdrawal symptoms [5].

Healthy vaginal microbiota is mainly colonized by *Lactobacillus* spp., which synthesizes lactic acid and other products that provide local protection against pathogens [6]. The replacement of the lactobacilli by anaerobic pathogens facilitates its ascent to the amniotic cavity and triggers an inflammatory response characterized by the production of cytokines and prostaglandins, ultimately inducing the labor-related events of myometrial contractility, cervical effacement, and rupture of the amniochorion membranes [7]. Although treatment for vaginal dysbiosis has not yet been proven effective in preventing PTB in late pregnancy, the condition is easily diagnosed by bacterioscopy, and the maintenance of eubiosis from the early stages of pregnancy may favor timely, adequate outcomes.

Another well-established risk factor for PTB is the length of the uterine cervix. A cervical length of less than 25 mm between the 16th and 24th gestational weeks is a strong independent predictor of spontaneous PTB. The risk of PTB in these cases is estimated at 25–30% in women with no history of PTB and up to 35% in pregnant women who have previously presented PTB. If the length is under 15 mm, the risk of PTB reaches 50%. In fact, several authors indicate the need for screening cervical length in this period via transvaginal ultrasound [8,9]. The management of cervical shortening (CS) includes the topical administration of progesterone, the use of pessary, and cerclage. A recent meta-analysis detected a significant reduction in the rate of extreme prematurity (< 33 weeks of gestation, < 2,500 grams birth weight) in pregnant women with CS (< 25 mm) who used intravaginal progesterone daily [9].

A common factor for the aforementioned conditions is the possibility of implementing preventive measures. Identifying risk factors for PTB early and before the development of irreversible clinical symptoms (e.g. cervical dilation, intraamniotic infection, oxidative damage associated inflammation) enables a personalized approach to patient care, aiming to reduce the risk of preterm birth and its sequelae. Thus, the primary aim of this study protocol is to reduce PTB in pregnant women from Health Units in the city of Jaú - SP, Brazil by implementing a low-cost bundle to assess and manage major modifiable risk factors for PTB. The secondary aim is to demonstrate the feasibility of our implementation protocol.

## Methods

### Study design

This is the protocol of an ongoing implementation study with a quasi-experimental controlled trial design conducted with pregnant women from primary health care units in the municipality of Jaú. The city of Jaú, located in the central region of the state of São Paulo, has a population of 151,881 inhabitants and 16 Basic Health Units (UBS) and Family Health Units (USF), in addition to a high-risk pregnancy clinic, Gestar, where this project is implemented.

The 16 UBS/USF were considered clusters and will be included in the study at different stages, according to the stepped wedge model, in which the clusters are gradually transferred to the intervention group at regular intervals until all have been transferred. This design is particularly useful in situations where the intervention cannot be implemented simultaneously for all units due to time, logistics, or ethical constraints [10]. In the first phase, eight of these clusters were randomly selected using a simple randomization process to receive the intervention, focusing on pregnant women during their first trimester. Over time, the remaining clusters will be randomly assigned to transition into the intervention group at regular intervals, using the same simple randomization method, ensuring that by the end of the study, all clusters will have received the intervention (Figure 1). This approach allows for a structured, phased implementation of the intervention, accommodating logistical and ethical constraints, and enables the comparison between clusters that have and have not yet received the intervention during the initial stages of the study.

**Figure 1. f0001:**
[figure not shown]
Temporal flowchart of cluster inclusion (health units) in the quasi-experimental design study.

During the first 18 months, all first-trimester pregnant women from eight randomized UBS/USF (clusters) are being included. In the next step of the study, 2 UBS/USF per month will be included until all primary care units (clusters) in the municipality are included, as demonstrated in Figure 1.

All pregnant women of eligible gestational age from the eight initially randomized health units were systematically invited to participate in the study and referred to Gestar. Cluster randomization was performed using a randomization tool (https://www.random.org/). Allocation was concealed and known exclusively by the coordinating researcher until implementation, minimizing the risk of selection bias. All participants included in the study will be monitored until the gestational outcome through three appointments, one in each gestational trimester. The inclusion criteria for the study are singleton pregnancy and gestational age between 11 weeks and 13 weeks and 6 days at the first appointment, defined by ultrasound. Pregnancies with fetal death and those attending fewer than two study appointments (first and second trimester) will be excluded from the study.

Considering the intervention aims to reduce the preterm birth rate from 18% (baseline rate, DataSUS) to 11.5% (São Paulo state rate = target rate), with 95% confidence, 5% margin of error, and 80% statistical power, the minimum sample size calculated is 201 patients (SAS 3.0 software). Adjusting the sample size to account for cluster effects (DE = 1+(m − 1)×ICC, where DE: design effect; mean cluster size: *m* = 20; intra-cluster correlation coefficient: ICC = 0.01), the conventional individual-based sample of 201 increased to 240. Considering a 20% loss to follow-up, the final sample size will be 300 participants.

To reduce cross-contamination, clinical procedures are centralized at a reference site (Gestar), and the distribution of printed and digital protocols to the Health Units are restricted until activation. A 2-week operational wash-in with adherence monitoring was implemented.

This project was approved by the Research Ethics Committee of Unoeste – Universidade do Oeste Paulista (CAAE 63,623,922.70000.5515). All patients involved will be informed about the research and sign the informed consent form.

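### The trial enrols singletons only, but its 18% and 11.5% reference rates and its general-population comparator are not limited to singletons, so that comparison favours the bundle through case mix

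*Protocol article*

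**What the plan says.** **Eligibility (Methods, Study design).** "The inclusion criteria for the study are singleton pregnancy and gestational age between 11 weeks and 13 weeks and 6 days", the latter at the first appointment. Pregnancies with fetal death, and women who attend fewer than two study visits (first and second trimester), are then excluded.

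**Planning rates (same section).** The sample size rests on an intervention meant to "reduce the preterm birth rate from 18% (baseline rate, DataSUS") to "11.5% (São Paulo state rate = target rate"). Neither figure is said to be restricted by plurality or by time of booking.

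**Related rates elsewhere.** The Background words its figures as unrestricted: for the state, "12% of births in 2023 were preterm"; for the municipality, "where this adverse outcome affected 13.5% of all pregnancies". The Abstract describes the setting as one "where PTB prevalence ranges from 13,4% to 18"%. The article gives no singleton-specific rate anywhere.

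**Comparison (Methods, Analysis plan).** The main outcome is to be compared between study participants and the general population. The same section takes the primary effect estimate from a mixed-effects logistic model with a random cluster intercept and fixed period effects. The article therefore describes two comparisons, and the population one carries no eligibility restriction.

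**The concern.** Multiple pregnancies are delivered preterm much more often than singletons. A rate over all births therefore exceeds the rate in the singletons who can enter this trial. If participants are set against an all-births figure, their rate will be lower even if the bundle does nothing.

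The second exclusion rule may add to this. A woman who delivers before her second-trimester visit cannot reach two appointments and leaves the cohort, but her birth stays in population statistics. The restriction to women first seen by 13+6 weeks is a further difference. The article does not say in which direction it acts.

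What is at stake is the reading of the result. A crude contrast with 18% or with municipal births would mix a bundle effect with an eligibility effect, and the reader could not separate them.

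**Working it through.** **1. The plan's own figures.** Design effect: 1 + (20 − 1) × 0.01 = 1.19. Then 201 × 1.19 = 239.2, rounded up to 240, and 240 / 0.8 = 300. These steps reproduce. The starting 201 does not reproduce as a two-group comparison of 18% with 11.5% (467 per arm, two-sided 5%, 80% power). Only one-sided, one-sample variants against a fixed 18% come close: 207 with a continuity correction, or an exact binomial test at one-sided 5%, with power 77.7% at n = 201 and 82.8% at n = 202. That is a separate problem. It matters here only because it suggests that a fixed reference rate may have been in mind.

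**2. Converting an all-births rate to singletons.** Let *s* be the share of multiples among births and *r* their preterm rate. Then

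singleton rate = (overall rate − *s* × *r*) / (1 − *s*).

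The article gives neither *s* nor *r*, so both are assumptions. The main range is *s* = 2 to 3% and *r* = 50 to 65%; the wider range is *s* = 1 to 4% and *r* = 50 to 70%. That 18% and 11.5% cover all births is also an inference.

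Example: (0.18 − 0.03 × 0.65) / 0.97 = 0.1605 / 0.97 = 16.55%.

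| *s*, *r* | 18% becomes | Shift (points) | Shift / 6.5 | 11.5% becomes | Difference, both converted |
|---|---|---|---|---|---|
| 1%, 50% | 17.68% | 0.32 | 5% | 11.11% | 6.57 |
| 2%, 50% | 17.35% | 0.65 | 10% | 10.71% | 6.63 |
| 2%, 60% | 17.14% | 0.86 | 13% | 10.51% | 6.63 |
| 3%, 65% | 16.55% | 1.45 | 22% | 9.85% | 6.70 |
| 4%, 70% | 15.83% | 2.17 | 33% | 9.06% | 6.77 |

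**3. Effect on a comparison with a fixed 18%.** The article does not specify such a test, so this only illustrates the size of the bias. Suppose 201 singletons are tested against 18% and the bundle has no effect. The nominal 2.5% chance of a significant fall becomes about 4.7% in the 2%, 60% case, and 3.2% to 11.1% over the wider range.

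**4. Effect on the planned contrast.** With both rates converted, the difference is 6.5 / (1 − *s*), as in the last column. It grows slightly. The two-sided two-group requirement falls from 467 per arm to 424 in the 2%, 60% case (372 to 448 over the wider range). If only the baseline is converted and 11.5% is kept, it rises to 604 (512 to 986), but that puts the two rates on different bases.

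**The case against.** The strongest reply is that the primary estimate comes from the mixed model, and the Study design section describes comparison with clusters that have not yet received the intervention. If the control women are singletons under the same criteria, the case-mix difference cancels. This stands. The exposure is confined to the general-population comparison and to any informal reading against 18% or 11.5%.

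A reader might infer more: that part of the planned 6.5-point reduction is supplied by the eligibility rule, or that the sample size rests on an inflated difference. The documents do not support that. If both rates are all-births rates, converting both leaves the difference slightly larger. Likewise, the gap between the Background's 13.5% and the 11.5% target appears to shrink only if one side is converted. At *s* = 3% and *r* = 65% the two become 11.91% and 9.85%, still 2.06 points apart. Nor does the article make reaching 11.5% a criterion of success.

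Two further limits stand. The size rests wholly on assumed inputs. It is also small beside the 4.5-point gap between the 18% baseline and the 13.5% municipal rate in the Background, and beside the labelling of 11.5%, which the Background attaches to Brazil while giving 12% for the state. Those are separate matters, and resolving them would not put the reference rates on a singleton basis.

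**Conclusion.** The point holds for the comparison, not for the planned difference. As written, the cohort is restricted to singletons while the reference rates and the population comparator are not, and the Analysis plan sets one against the other. If 18% is an all-births rate, eligibility alone lowers the expected rate by 0.65 to 1.45 points (10 to 22% of 6.5) under the main assumptions, and by 0.3 to 2.2 points (5 to 33%) under the wider ones. The direction is clear for multiples; the exact size cannot be had from the article. The contribution of late booking and of the two-visit rule cannot be sized at all. The mixed-model estimate is free of this bias provided its control women meet the same criteria.

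**What to change.** **Analysis plan.** State that any general-population or control comparator is limited to singleton births and, as far as the records allow, to pregnancies that meet the trial's other inclusion and exclusion criteria (gestational age at first visit, fetal death, attendance).

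**Study design, sample size.** Restate both the 18% and the 11.5% on a singleton basis with the source query described. Convert both, not one.

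**Cost.** One re-query of the birth data by plurality, and by time of first prenatal visit where recorded, plus a wording change. The stated baseline and target will both be lower. The planned difference, and the sample size that follows from it, should change little from this correction alone. Matching on attendance may not be possible in routine records; if so, say so as a limitation of the population comparison.

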Below is a detailed description of each component of the intervention:(1) First Trimester (11 to 13 weeks and 6 days): Assessment and Smoking Intervention.**Sociodemographic and Clinical Assessment**: During the first trimester, participants undergo an initial interview to collect personal, social, and clinical information. This includes family and obstetric history, as well as smoking status.**Smoking Cessation Support**: Pregnant women identified as smokers who are willing to quit are provided with a comprehensive smoking cessation program. This includes referral to the city’s smoking prevention program, which is conducted at the Alcohol and Drug Psychosocial Care Center (CAPS-AD).The smoking intervention involves an initial interview and adjuvant treatment with auricular acupuncture. This technique uses pressure points in the ear to help reduce anxiety and withdrawal symptoms associated with smoking cessation.Acupuncture sessions are conducted every 15 days, where seeds are placed on specific points in the ear to stimulate them. Cotton and 70% alcohol are used to clean the ear, an auricular pressure gauge is used to locate the points, and mustard seeds with micropore are placed for acupressure of the selected points. The patients are instructed to stimulate these points themselves three times daily. Auriculotherapy is delivered by a trained and certified professional. Patient engagement is monitored by tracking attendance, with the number of appointments systematically recorded in the medical records.If necessary, group sessions with psychological support are provided at CAPS-AD, and pharmacological treatment, such as nicotine patches, may be used for gradual dose reduction to alleviate withdrawal symptoms.2. **Second Trimester (20 to 23 weeks and 6 days): Cervical Length Monitoring and Infection Treatment**.**Cervical Length Screening**: Between 20 and 24 weeks of gestation, all participating women undergo a transvaginal ultrasound to measure cervical length, a critical indicator of the risk for PTB.The measurement is taken with the patient in the lithotomy position, using a transvaginal probe to assess the distance between the internal and external orifices of the cervical canal. Women are instructed to empty their bladder before the ultrasound evaluation.Three consecutive measures are taken and the smallest value is considered. If a cervical length of less than 25 mm is detected, the woman is diagnosed with cervical shortening.Women diagnosed with cervical shortening are prescribed 200 mg of vaginal progesterone daily until 36 weeks of gestation, aiming to reduce the risk of PTB. For these women, the measurement is repeated biweekly for follow-up and monitoring treatment adherence.For cases of severe cervical shortening, such as lengths below 15 mm, cerclage – a surgical procedure to reinforce the cervix – is considered, depending on the patient’s clinical history and ongoing evaluations.**Investigation and Treatment of Infections**: During the same trimester, women are also screened for lower genital tract infections using molecular tests for *Chlamydia trachomatis* and *Neisseria gonorrhoeae*. These investigations are performed at this time due to the less friable nature of mid-trimester cervices in comparison to the first trimester of pregnancy.The assessment includes a complete gynecological examination with swabs for Gram staining, vaginal pH measurement, and cytobrush sampling collection for PCR analysis of cervical infection using the automated Cobas® 4800 CT/NG v2.0.Identified infections are treated according to the local clinical protocols to ensure the health of both the mother and the fetus.

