### Analysis plan

The main outcome of interest is gestational age at birth, based on first-trimester ultrasound, to be compared between the participants of the study and the general population. For the analysis, gestational age will be treated as categorical data (preterm birth vs. term birth). The primary analysis will follow the intention-to-treat principle: participants will be analyzed according to the assignment of their cluster at the time of inclusion. Secondary analyses will consider gestational age at delivery (continuous, in days) and other perinatal outcomes.

Secondary outcomes include the percentage of pregnant women included, the percentage of complete follow-up, percentage of adherence to prescribed treatments, and neonatal outcome (Apgar score, birth weight, and length of stay in the Intensive Care Unit). Descriptive statistics will be performed to analyze clinical, biological, and sociodemographic data of the studied population. Vaginal microbiota status across the trimesters will be compared using the Chi-square test.

Logistic regression will be performed to evaluate the role of the protocol in reducing PTB. To minimize multiplicity in the analysis and interpretation, covariates for adjustment such as parity, maternal age, and socioeconomic status will be included. The primary effect estimate will be obtained from mixed-effects logistic regression models including a random intercept for cluster and fixed effects for period and pre-specified baseline covariates (maternal age, parity, socioeconomic status). Additional per-protocol analyses will be performed as sensitivity analyses and will include participants who received the defined intervention components. Missing data in covariates will be handled using multiple imputations (MICE) under a missing-at-random assumption. The level of significance adopted for the tests used will be 5%, using *Prism* 5.0 (GraphPad Software).

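### Excluding women after enrolment for fetal death or a missed second-trimester visit contradicts the intention-to-treat primary analysis and can lower the preterm rate among participants without any effect of the bundle

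*Protocol article*

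**What the plan says.** Methods, Study design (text after Figure 1), sets the entry window: "gestational age between 11 weeks and 13 weeks and 6 days at the first appointment, defined by ultrasound". It then adds: "Pregnancies with fetal death and those attending fewer than two study appointments (first and second trimester) will be excluded from the study". Interventions places the appointment that decides the attendance rule: "Second Trimester (20 to 23 weeks and 6 days): Cervical Length Monitoring and Infection Treatment".

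The Analysis plan says: "The primary analysis will follow the intention-to-treat principle: participants will be analyzed according to the assignment of their cluster at the time of inclusion". It also plans a per-protocol analysis: "Additional per-protocol analyses will be performed as sensitivity analyses and will include participants who received the defined intervention components". Multiple imputation is named for covariates only.

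The comparator is described in two ways. The Analysis plan has gestational age at birth "to be compared between the participants of the study and the general population"; Study design says the staged roll-out "enables the comparison between clusters that have and have not yet received the intervention during the initial stages of the study". The only women described as invited and attending study appointments are those of the randomised, activated units, who are referred to the reference clinic (Gestar).

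Interventions gives interviews and medical records as the source of pregnancy outcome. The sample-size paragraph ends: "Considering a 20% loss to follow-up, the final sample size will be 300 participants".

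**The concern.** An eligibility criterion has to be known when the woman enters. Fetal death and a missed second-trimester visit are not. To be counted, a woman must still be pregnant, and still attending, some 6 to 13 weeks after inclusion, and must not have a fetal death at any later time. That selects on survival of the pregnancy and on adherence, and the primary outcome (preterm versus term birth) is closely tied to the first of these.

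If such a filter works on participants but not on the women they are compared with, the participants' preterm rate can fall although the bundle does nothing. The rule defines the primary analysis set, so covariate adjustment and imputation of covariates do not repair it.

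**Working it through.** **1. The passages side by side.**
- Inclusion: 11w0d to 13w6d.
- Deciding visit: 20w0d to 23w6d. The shortest gap is 13w6d to 20w0d = 6w1d; the longest is 11w0d to 23w6d = 12w6d.
- Primary analysis: by cluster assignment at inclusion, under intention-to-treat.
- Exclusion: by attendance at the deciding visit and by fetal death, both after inclusion.

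A woman included at 12 weeks who does not attend at 20 to 23w6d and delivers at 34 weeks belongs in the primary analysis under the Analysis plan and is outside the study under Study design. This needs no arithmetic.

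**2. On which side does the filter act?** An attendance rule can apply only where there are study appointments. These are described only for women from activated units. No appointment schedule is described for units not yet exposed or for the general population. One-sidedness of the attendance rule is therefore an inference, though a strong one. Fetal deaths could be removed from comparator records as well; the article does not say whether they are.

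**3. The plan's own loss figure.** Design effect = 1 + (20 − 1) × 0.01 = 1.19; 201 × 1.19 = 239.2, rounded up to 240; 240 / (1 − 0.20) = 300. These steps reproduce. The allowance is 300 − 240 = 60 women.

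**4. Possible size of the distortion with no true effect.** Inputs: true preterm rate p = 18% (the plan's baseline); target fall 18 − 11.5 = 6.5 points; share excluded f; risk of excluded women k times that of those retained. Neither f nor k is given by the documents. I borrow f = 20% from the loss allowance and vary k. Because p = (1 − f)r + f·k·r, the rate among those retained is

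r = p / (1 − f + f·k).

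| k | r at f = 20% | Apparent fall (points) | Share of 6.5 points |
|---|---|---|---|
| 1 | 0.18/1.00 = 18.0% | 0 | 0% |
| 1.25 | 0.18/1.05 = 17.1% | 0.9 | 13% |
| 1.5 | 0.18/1.10 = 16.4% | 1.6 | 25% |
| 2 | 0.18/1.20 = 15.0% | 3.0 | 46% |

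In counts, the last row is 54 preterm births among 300 women, of which 18 fall in the 60 excluded (30%) and 36 in the 240 retained (15%).

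A smaller excluded share gives less bias. At k = 2, f = 10% gives 0.18/1.10 = 16.4% and f = 5% gives 0.18/1.05 = 17.1%.

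**5. Is the second visit needed to know the outcome?** No. Medical records are already an outcome source, so gestational age at birth can be sought for women who stop attending.

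**The case against.** Several objections have weight.

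- **One-sidedness.** A reader might infer that both exclusions strip high-risk pregnancies from the intervention side only. The documents do not support that for fetal deaths: the article does not say how comparator data are obtained or whether fetal deaths are counted there. Very early losses may also be absent from a population birth rate, which would shrink that part of the bias.
- **Risk of non-attenders.** The documents do not say that women who miss the second visit have a higher preterm risk. If their risk equals that of the others (k = 1), there is no bias. The rule can lower the rate; it need not.
- **The 20%.** It is a loss-to-follow-up allowance, and the article does not equate it with exclusion by rule. Some of those women may have no obtainable outcome, and a change of rule would not recover them.
- **Per-protocol set.** A reader might infer that this analysis removes preterm births by construction, because some components run into the third trimester. The article does not say that all components must have been received, and the detailed definition may stand in a document not shown. The analysis is also openly labelled a sensitivity analysis. Only a caution remains.
- **Retaining fetal deaths.** Counting fetal deaths and early losses among participants alone, against a comparator built on births, would bias against the bundle. The remedy must bind both sides.

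These points limit the direction and size of the bias. They do not reconcile the two rules. One could call the set a modified intention-to-treat population, but the article does not, and its stated principle is assignment at inclusion.

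**Conclusion.** The contradiction between the exclusion rule and the intention-to-treat statement is certain, because the article states both rules. It should be resolved before analysis, since it determines who is in the primary set.

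That the attendance filter acts mainly on the intervention side is probable, by inference from where study appointments are described. Its direction would then tend to favour the bundle if non-attenders carry higher risk. The size cannot be determined from the documents. Under an 18% true rate, no effect, one-sided removal of 20% and a relative risk of 1 to 2 in those excluded, the spurious fall is 0 to 3.0 points, or 0 to 46% of the 6.5-point target, and less if fewer women are excluded. For fetal deaths, the finding is that the handling on the comparator side is unstated, not that it is shown to differ.

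The per-protocol analysis is a secondary matter. It again selects on what happens after inclusion, so it cannot test whether the primary result is robust to this selection.

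**What to change.** 1. Delete the attendance exclusion from the primary analysis set. Analyse every eligible woman included at 11 to 13w6d by her cluster's assignment at inclusion.
2. Take gestational age at birth from delivery or medical records whatever her attendance.
3. Define the handling of fetal deaths and early losses once and apply it identically to participants and comparator, for example the same live-birth restriction or the same gestational-age threshold on both sides, with the alternative as a sensitivity analysis. The Background defines preterm birth only by an upper limit of 37 weeks, so a lower limit needs stating.
4. Report attendance as a feasibility outcome. Completeness of follow-up and adherence are already secondary outcomes.
5. In the per-protocol set, count only components due before the woman's delivery, since requiring later ones would remove early births. Do not present this analysis as a check on the selection described here.

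Cost: changes of wording, some tracing of records for non-attenders in an ongoing study, and a possibly less favourable estimate. Women whose outcome cannot be found remain missing and should be reported as such.
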